### Sample size

Sample size and power calculations for the study are based on the following assumptions: two-sided log-rank test; α = 0.05; randomization ratio of 1:1. The sample size calculation is based on the expected change in 6MWT distance at week 24. In another study, the mean difference between groups for the change in 6MWT distance from baseline at week 24 was 40 m with a standard deviation (SD) of 70 m [18]. Based on these assumptions, a sample of 62 subjects per group (124 in total) are required to detect a mean treatment effect of at least 40 m at week 24 with 80% power at a two-sided significance level of 5%, allowing for 20% drop-out.

### Criteria for subject withdrawal

#### Withdrawal from the trial

Participants have the right to withdraw from the study at any time without having to give a reason. The investigator also has the right to withdraw patients from the study drug in the event of inter-current illness, adverse events, serious adverse events, suspected unexpected serious adverse reactions, protocol violations, or administrative or other reasons. Patients who refuse to undergo any form of follow-up are required to leave the study. For study participants who withdraw from the study, an eligible replacement will be recruited if the study is still recruiting.

#### Withdrawal from the medicinal product being investigated

Withdrawal from the medicinal product being investigated means that patients randomized to the intervention group discontinue levothyroxine under the guidance of non-investigators. According to the study, patients will be suspended from levothyroxine supplementation if TSH levels are less than the normal level and/or FT4 is greater than the upper limit of normal; however, this is not a withdrawal from medication. The post-test results will be used to determine whether the patient continues taking levothyroxine. Patients who stop taking levothyroxine are classified as withdrawn from the medication. Regarding adverse reactions during treatment, the clinical event committee will confirm whether the reactions are related to the study drug and intervention medication will be stopped.

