### Dosage and administration of levothyroxine

Levothyroxine will be administered at an initial dose of 12.5 μg once daily and will be titrated until TSH is within the reference range. All the participants will be required to have their thyroid function re-assessed at 4, 8, and 12 weeks to regulate the dosage of levothyroxine, whereas the thyroid status of those in the control arm will be only reviewed and recorded. Investigators will adjust the dosage of levothyroxine primarily based on TSH levels. Specifically, if TSH levels remain above the upper limit of the normal value, 12.5 μg/d of levothyroxine will be added. If TSH levels return to the normal range, the dosage of levothyroxine will be maintained. If TSH levels are below the lower limit of the normal value, the investigator will stop the levothyroxine prescription and thyroid function will be re-assessed 2 weeks later for further intervention (subjects remain in the thyriod hormone replacement therapy (TRT) group with regular thyroid function re-test and corresponding levothyroxine treatment until their TSH levels increase again). Patients who receive levothyroxine but have consistently elevated TSH levels during the 24 weeks will still be considered as “treated” and analyzed in the TRT group. In addition, the percentage of these patients in the TRT group will be calculated and reported, indicating the effectiveness of our conservative titrating strategy for subclinical hypothyroidism. However, these metrics are not the primary or secondary study endpoints. A flow chart of the study is provided in Fig. 1.

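### The dosing steps and the withdrawal section conflict on levothyroxine when FT4 is high and TSH is not low, and the opening definition of drug withdrawal leaves out investigator-led stops.

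*Protocol article*

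**What the plan says.** Protocol article, Dosage and administration of levothyroxine. The governing sentence is "Investigators will adjust the dosage of levothyroxine primarily based on TSH levels". Three steps follow:

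- A further increment is added "if TSH levels remain above the upper limit of the normal value".
- For a TSH back in range: "If TSH levels return to the normal range, the dosage of levothyroxine will be maintained".
- For a low TSH: "If TSH levels are below the lower limit of the normal value, the investigator will stop the levothyroxine prescription", with a re-test two weeks later.

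FT4 appears in none of these steps.

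Protocol article, Withdrawal from the medicinal product being investigated. This section presents as a rule of the study that "patients will be suspended from levothyroxine supplementation if TSH levels are less than the normal level and/or FT4 is greater than the upper limit". It adds that such a suspension does not count as withdrawal from medication, and that the re-test decides whether the patient continues.

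The same section opens by defining withdrawal from the drug as the case in which "patients randomized to the intervention group discontinue levothyroxine under the guidance of non-investigators". After the suspension rule it says: "Patients who stop taking levothyroxine are classified as withdrawn from the medication". It ends by providing for the drug to be stopped for adverse reactions, with a committee confirming whether they are related to it.

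Protocol article, Withdrawal from the trial. "The investigator also has the right to withdraw patients from the study drug", and adverse events are among the grounds listed.

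**The concern.** There are two separate problems.

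The first concerns patient handling. For certain laboratory results, one section tells the investigator to keep or raise the dose and another tells the investigator to suspend it. Five centres titrate from this text, the population has systolic heart failure, and the protocol lists malignant arrhythmia, aggravated heart failure and hyperthyroid crisis among its serious adverse events. A suspension rule for high FT4 should not depend on which page is open.

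The second is smaller and concerns reporting. If drug withdrawal means only a stop guided by someone other than an investigator, a stop that the investigator orders for an adverse event is not a withdrawal. A discontinuation count built on that definition could leave out stops that bear directly on tolerability, in a trial that sets out to study efficacy and safety.

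**Working it through.** No figure in the plan depends on this point. The sample size (62 per group, 124 in total) uses neither FT4 nor discontinuation by reason. The check is therefore a comparison of texts.

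**Step 1: dose action for each pair of results.** The dosage column applies the three TSH steps as written. The withdrawal-section column applies its *and/or* condition, under which either result suffices.

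| TSH | FT4 | Dosage section | Withdrawal section | Compatible? |
|---|---|---|---|---|
| low | not high | stop, re-test | suspend | yes |
| low | high | stop, re-test | suspend | yes |
| normal | not high | maintain | no suspension | yes |
| normal | high | maintain | suspend | **no** |
| high | not high | increase | no suspension | yes |
| high | high | increase | suspend | **no** |

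Four of the six cells agree and two do not. In one of the two the difference is maintain versus suspend; in the other it is increase versus suspend. Both need FT4 to rise above its limit after randomization, because eligibility requires FT4 within the reference range.

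The dosage section also describes the period after a stop in terms of TSH rising again. That does not fit a patient suspended for FT4 whose TSH was never low.

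**Step 2: which stops count as drug withdrawal.**

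| Kind of stop | Opening definition | Later sentence on patients who stop |
|---|---|---|
| Guided by a non-investigator | withdrawal | withdrawal |
| Ordered by the investigator for an adverse event | not withdrawal | withdrawal |
| Protocol-driven temporary suspension | not withdrawal | expressly exempted just before |

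The second row is the conflict. The third row is settled by the text: the exemption comes first, so the later sentence can be read as covering patients who stop for good.

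**Step 3: size.** The documents give no rate of high FT4 with TSH not low, and no rate of investigator-led stops. The number of patients affected cannot be computed, and any percentage applied to the 62 patients per group would be a guess.

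**The case against.** The best defence of the dosing text is the qualifier *primarily*. On that reading the dosage section describes routine titration and the withdrawal section adds a safety suspension, so the first is incomplete and not opposed to the second. This has some force: a reader might infer that the dosage section bases every action on TSH alone, and the text does not go that far. But the steps that spell out the general sentence have no FT4 exception and do not refer to the other section. An investigator who follows them literally maintains or increases the dose where the other section suspends it. The qualifier softens the conflict without removing it.

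It is also fair that the disagreement is confined to two cells, and that only one of them sets an increase against a suspension.

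On withdrawal, a reader might infer that the later sentence makes every patient who ever stops a withdrawal. The text does not say *every*, and the sentence follows the exemption for suspensions and the re-test step, so permanent stops are a natural reading. That reading still leaves the opening definition excluding permanent stops ordered by an investigator.

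The harm from this second problem is limited. No discontinuation rate is named as an endpoint or planned analysis. Serious adverse events are to be recorded and compared between groups, and patients are analysed as randomized whatever treatment they received. Reason codes may well stand in the full protocol or case report form, which are not shown. All of this lowers the weight of the reporting point, but none of it reconciles the two sentences.

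**Conclusion.** The point holds in two parts of unequal weight.

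The main part is that the dosage and withdrawal sections give incompatible instructions for normal TSH with high FT4 and for high TSH with high FT4: two of six combinations. Patients with the same results could be handled differently. This rests only on reading the dosing steps as written and *and/or* in its ordinary sense.

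The lesser part is that the opening definition of drug withdrawal excludes investigator-led stops for adverse events, while a later sentence in the same section takes them in. Any reported discontinuation count could omit them.

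Two stronger conclusions are not supported. A reader might infer that practice will differ by centre; the documents describe no centre-level practice and show only that it could differ. A reader might also infer that the primary comparison is affected; assignment to groups in the intention-to-treat analysis does not depend on the withdrawal label, and the sample size does not use it. The number of patients concerned is unknown. No view is taken here on which clinical rule is right.

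**What to change.** 1. Reconcile the dosage section and the withdrawal section into a single rule that says explicitly whether FT4 counts, and cover both conflicting cells. The sponsor's clinicians decide the content. Word the step after a suspension so that it fits whatever triggers the rule allows.
2. Use one definition of drug discontinuation that includes investigator-led stops. For each stop, record who stopped the drug and why. Report protocol-driven temporary suspensions as a separate category.

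The cost is a clarification of wording and, if not already present, a field in the electronic case report form for who stopped the drug and the reason. No change to sample size or to the primary analysis is needed. Whether FT4 is measured at each follow-up visit should be confirmed in the assessment schedule, which is not shown; the withdrawal section presupposes that on-treatment FT4 results exist. Recruitment was in progress when the article was written, so a clarification should go to all five centres, and stops already recorded should be reclassified under the single definition.

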#### Premature withdrawal of subjects from the trial

The investigator recognizes the need to terminate the study taking in to consideration a patient’s medical condition. Regarding subjects who do not want to continue the clinical study, the investigator will propose study termination.

#### Definition of completion of trial for subjects

A subject will be considered to have completed the study if he or she completed all assessments and procedures during the follow-up period of 24 weeks for primary endpoint events. All randomized patients will undergo a follow-up assessment (from the randomization to 24th week) to determine exercise capability, survival status, and hospitalization data. If the subject dies during this period, the study coordinator and/or principal investigator should make every effort to obtain the details of the subject’s death from the relevant hospital or physicians and/or relatives. If confirmation of death is not available by these means, the study coordinator and/or principal investigator will attempt to confirm the subject’s death through a death index search (through the Chinese household registration system).

### Participant safety and adverse events

All serious adverse events, including aggravated HF, malignant arrhythmias, myocardial infarction, stroke, severe hepatic and renal dysfunction, sudden death, and hyperthyroidism crises occurring after randomization and before hospital discharge, are to be recorded on the study forms and will be the subject of comparisons between the randomized study treatment groups. Any serious adverse events that are thought by a patient’s own doctors or the study team to be due to the study treatment (i.e., serious adverse reactions) with a reasonable probability are to be reported to the Fuwai trial coordinating center in an expedited fashion.

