## Methods/design

### Patient selection

Eligible participants will be identified from the cardiology units of five study centers (Fuwai Hospital, Beijing LuHe Hospital, The Second Hospital of Tianjin Medical University, The First Hospital of Hebe Medical University, Henan Provincial People’s Hospital). All individuals will have their thyroid function checked within 24 h of admission to the hospital or clinical visit. Eligible patients will meet the following inclusion criteria: (1) 18 years or older, (2) systolic HF with NewYork Heart Association (NYHA) class II–III, (3) left ventricular ejection fraction ≤ 40% by echocardiography during screening and randomization, (4) subclinical hypothyroidism (TSH > ULN, < 10 mIU/mL + FT4 level within reference range, (5) receiving standard therapy for chronic heart failure (CHF), reaching target dose or maximum tolerable dose, and (6) provide informed consent. The major exclusion criteria include acute HF or acute exacerbation of chronic HF within the past 2 weeks; scheduled cardiac resynchronization therapy or heart transplantation; history of malignant tumor or life expectancy under 12 months; currently taking medications that may affect thyroid function (LT4, carbimazole, propylthiouracil, amiodarone, lithium); pregnancy and lactation period; participation in another clinical trial within the past 30 days; contraindication or intolerance to evidence-based therapy for CHF, such as beta-blocker, angiotensin-converting enzyme inhibitor, or angiotensin receptor blocker; known hypersensitivity to the trial treatment(s) or diluents (when applicable), including placebo or other comparator drug(s); severe renal dysfunction (estimated glomerular filtration rate ≤ 30 ml/min/1.73 m^2^) or significant hepatic impairment (serum GPT > 120 U/L); and any disorder which, in the opinion of the investigator, might jeopardize a subject’s safety or compliance with the protocol.

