### Follow-up measurements

Clinical follow-up will be performed at weeks 4, 8, 12, and 24 after enrolment. The schedule for visits and evaluation of the subjects is presented in Table 1.

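### Serious adverse events are recorded and compared only up to hospital discharge, which contradicts 24 weeks of treatment and follow-up and has no meaning for patients enrolled from clinic

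*Protocol article*

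**What the plan says.** The section Participant safety and adverse events of the Protocol article names a set of serious adverse events and gives their window. The list ends with "sudden death, and hyperthyroidism crises occurring after randomization and before hospital discharge, are to be recorded on the study forms". The same sentence gives their use: they "will be the subject of comparisons between the randomized study treatment groups". The next sentence adds expedited reporting of SAEs that a patient's doctors or the study team attribute to study treatment. It states no end date.

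Other sections describe a longer course:

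- Follow-up measurements: "Clinical follow-up will be performed at weeks 4, 8, 12, and 24 after enrolment".
- Dosage and administration of levothyroxine: thyroid function is "re-assessed at 4, 8, and 12 weeks to regulate the dosage of levothyroxine".
- Definition of completion of trial for subjects: "All randomized patients will undergo a follow-up assessment (from the randomization to 24th week) to determine exercise capability, survival status, and hospitalization data".
- Patient selection: patients have "thyroid function checked within 24 h of admission to the hospital or clinical visit", so entry is possible from a ward or from a clinic.

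No visible section extends general SAE recording to week 24. Table 1, the schedule of assessments, is not legible in the copy reviewed.

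**The concern.** Safety is a stated aim of the trial alongside efficacy. A window that closes at discharge suits an inpatient treatment. Here the drug is started low, adjusted over three visits and continued for 24 weeks in patients with NYHA class II–III disease, so most exposure is likely to fall outside hospital. For a patient randomised from clinic the window cannot be applied at all.

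If sites follow the sentence, SAEs after discharge need not be entered on the study forms, and no later analysis can recover what was not recorded. Discharge is also a decision taken after randomisation. In an open-label trial, staff who know the allocation take it, so the length of observation could differ between arms. Recruitment is described as in progress, so events may already be going unrecorded.

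**Working it through.** The plan gives no figure for the SAE window or for length of stay, so there is none to reproduce. The sample size does not bear on this point.

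**Step 1. Share of the treatment period covered.**

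Inputs: follow-up of 24 weeks (Definition of completion), so 24 × 7 = 168 days; first scheduled dose check at week 4 (Dosage and administration), so 4 × 7 = day 28. Days from randomisation to discharge, *d*, are an assumption.

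Share covered = *d* / 168.

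| *d* (assumed) | Covered | Missed |
|---|---|---|
| 0 | 0.0% | 100.0% |
| 7 | 4.2% | 95.8% |
| 14 | 8.3% | 91.7% |
| 21 | 12.5% | 87.5% |
| 28 | 16.7% | 83.3% |

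The row *d* = 0 stands for a patient already discharged when randomised. That is plausible: the Randomization section puts two weeks of standard treatment first, and Patient selection excludes acute heart failure in the preceding two weeks. For a patient who was never admitted the window is undefined, which is not the same as 0%.

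**Step 2. Exposure after a dose increase.** The first scheduled increase is at day 28. The window contains exposure after it only if the patient is still in hospital beyond day 28.

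**Step 3. What other sections still capture after discharge.** The list in the safety section is set against the secondary endpoints and the follow-up of survival and hospitalisation to week 24.

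| Listed event | Compared between arms by another route? |
|---|---|
| Malignant arrhythmia | Yes, if it counts as severe arrhythmia in the secondary composite |
| Stroke | Yes, in the same composite |
| Sudden death | Yes, through survival status and cardiovascular death |
| Worsening heart failure | Only if it leads to readmission or cardiovascular death |
| Myocardial infarction | Only if it leads to readmission or cardiovascular death |
| Severe liver or kidney dysfunction | No; an admission might be noted, but neither composite counts it |
| Thyroid crisis | No; same reason |
| Any other SAE | No |

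The composites state no time point. The table takes them to run to week 24, in line with the follow-up.

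**Step 4. The expedited route.** It has no end date but covers only events attributed to treatment. Control patients receive no levothyroxine and the trial is open label, so this route cannot give an unselected comparison of the arms.

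**The case against.** The strongest reply is that the document plainly expects adverse events throughout treatment. Besides the secondary endpoints and the expedited route, it has a committee to judge reactions during treatment, a safety analysis set, and withdrawal from study drug for adverse events. The discharge limit then looks like a stray phrase, and Table 1 or the full protocol may already schedule SAE collection at each visit. This supports calling the problem an inconsistency and not a deliberate design. It does not remove it: the article states a specific window, and nothing visible overrides it.

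Two other readings of the sentence are possible. The limit might attach only to the last item, thyroid crisis. The whole-list reading is more natural, and the narrow one would still cut off the event most closely tied to the drug. Alternatively, discharge might mean discharge from any later admission. That would let in events at higher doses, but would still omit events managed outside hospital. The existence of these readings is itself a reason to rewrite the sentence.

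A reader might infer that the trial's safety results would look reassuring whatever levothyroxine does, or that malignant arrhythmia goes uncollected. The documents do not support either. An excess of severe arrhythmia, stroke, cardiovascular death or cardiovascular readmission should appear in the secondary endpoints. A reader might also conclude that every higher dose certainly escapes observation. That depends on a length of stay that the documents do not give.

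**Conclusion.** The point holds as a contradiction between the SAE window and the 24-week course of treatment and follow-up. If discharge falls within 28 days of randomisation, the window covers at most 16.7% of 168 days and no exposure after a scheduled increase. Both statements rest on that assumption and on discharge meaning the admission during or around which the patient was randomised. For clinic patients the window has no defined end.

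The damage is confined to the SAE comparison. What lacks an unselected between-arm comparison after discharge is mainly thyroid crisis, severe liver or kidney dysfunction, infarction or worsening heart failure without readmission, and SAEs outside the list. The primary endpoint is unaffected. The sentence should still be corrected, because it governs what is recorded for a stated aim of the trial.

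**What to change.** Reconcile Participant safety and adverse events with Follow-up measurements and Definition of completion of trial for subjects. Replace the discharge limit with: *from randomisation up to the week-24 visit or death, in both arms, whether or not study drug was stopped*. Collect SAEs at the existing visits at weeks 4, 8, 12 and 24, and base the between-group SAE comparison on that window. Check that the electronic case report form accepts SAEs throughout, and ask sites about unrecorded events in patients already enrolled.

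The cost is one amended sentence, a check of the form and more SAE forms to complete. No new visit is needed, and dosing and clinical management are unchanged.
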